## Abstract

**Background:**

Gynaecological cancers are diagnosed in over 1000 women in Wales every year. We estimate that this is costing the National Health Service (NHS) in excess of £1 million per annum for routine follow-up appointments alone. Follow-up care is not evidence-based, and there are no definitive guidelines from The National Institute for Health and Care Excellence (NICE) for the type of follow-up that should be delivered. Standard care is to provide a regular medical review of the patient in a hospital-based outpatient clinic for a minimum of 5 years. This study is to evaluate the feasibility of a proposed alternative where the patients are delivered a specialist nurse-led telephone intervention known as Optimal Personalised Care After Treatment for Gynaecological cancer (OPCAT-G), which comprised of a protocol-based patient education, patient empowerment and structured needs assessment.

**Methods:**

The study will recruit female patients who have completed treatment for cervical, endometrial, epithelial ovarian or vulval cancer within the previous 3 months in Betsi Cadwaladr University Health Board (BCUHB) in North Wales. Following recruitment, participants will be randomised to one of two arms in the trial (standard care or OPCAT-G intervention). The primary outcomes for the trial are patient recruitment and attrition rates, and the secondary outcomes are quality of life, health status and capability, using the EORTC QLQ-C30, EQ-5D-3L and ICECAP-A measures. Additionally, a client service receipt inventory (CSRI) will be collected in order to pilot an economic evaluation.

**Discussion:**

The results from this feasibility study will be used to inform a fully powered randomised controlled trial to evaluate the difference between standard care and the OPCAT-G intervention.

**Trial registration:**

ISRCTN45565436.

## Background

In the UK, gynaecological cancers including endometrial (c. 8500 per year), ovarian (c. 7000 per year), cervical (c. 3000 per year) and vulval (c. 1200 per year) cancer are retrospectively the fourth, fifth, twelfth, and twentieth most common cancer sites in women [1–4]. Over 1000 females are diagnosed and treated with gynaecological cancers each year in Wales (ovarian = 365, uterine = 539, cervical = 164) [5]. Three North Wales hospitals comprising Betsi Cadwaladr University Health Board (BCUHB) (Ysbyty Gwynedd, Ysbyty Glan Clwyd, and Ysbyty Maelor) serve a population of approximately 678,000 people [6], with 92 ovarian cancer, 107 endometrial cancer and 35 cervical cancer newly diagnosed in 2014 [7].

### Aims of follow-up

The aims of follow-up care include the management of patients’ physical and psychological morbidity and the prevention or early detection of local recurrence, distant metastases or appearance of second cancers [8, 9]. Follow-up care is routine for women who have completed treatment for gynaecological cancer but is not evidence-based. Currently, there is no agreement as to what follow-up care is effective, and there are no guidelines from The National Institute for Health and Care Excellence (NICE) as to what form or frequency of follow-up is appropriate after treatment for gynaecological cancer.

### Standard approach to follow-up

Following completion of treatment for gynaecological cancer, the traditional medical practice is to regularly review the patient in a hospital-based, outpatient clinic over a period of years. These regular reviews occur according to a locally or regionally agreed schedule for at least 5 years after completion of treatment. In addition to clinical review, patients may have blood tests, scans or other tests as required. Multiple unproven assumptions lie behind this standard approach to gynaecological cancer follow-up; one being that it will benefit the patient by detecting recurrence early, thus allowing effective treatment and improving survival, or alternatively will offer reassurance to the patient that all is well. There is however little evidence to support this approach. In general, early detection of recurrence is unlikely to improve survival if there is no intervention capable of producing a cure [10]. For the majority of gynaecological cancers, any treatment for recurrence is palliative and not curative. Whilst a few retrospective studies suggest that survival was improved when recurrent cervical or endometrial cancer was detected at routine follow-up rather than when symptoms develop [11–13], the majority of patients relapse with symptoms that would prompt reassessment even if the patient was not on routine review [14–17]. A randomised controlled trial (RCT) in ovarian cancer that assessed the value of detecting relapse early by using serum CA125 measurements as part of routine follow-up confirmed that whilst the test was able to detect pre-symptomatic recurrence, this did not lead to any survival benefit. It did however lead to an inferior quality of life due to further chemotherapy provision and more treatment-related morbidity [18]. This study again raises doubts about the value of detecting pre-symptomatic recurrence.

Patients may also receive false reassurance (when follow-up finds ‘no symptoms’) or they may wait for their next routine appointment to disclose symptoms [19] thus possibly delaying detection and appropriate symptom management. Furthermore, there is evidence that hospital-based, medical follow-up fails to address many of the broader needs that patients have following treatment for gynaecological cancers. Patients commonly report problems with anxiety and depression [20] and reduced health-related quality of life (QoL) [21], with specific problems including the physical effects of treatment such as distressing disturbance of bowel and bladder function, sexual relations and relationships, psychological health and employment problems [22, 23]. These issues are reflected in studies of patient-expressed needs. Female cancer patients tend to express more needs than male cancer patients and report less satisfaction with support generally [24, 25]. Gynaecological cancer patients have reported a high level of need for detailed information, information regarding how best to recover from surgery or to avoid recurrence and information regarding physiological and psychological issues [24, 26, 27]. There is evidence that doctors in routine follow-up clinics often fail to identify such problems and, if they do, they fail to address them effectively [28, 29].

Finally, the standard approach to follow-up burdens the health service with significant costs and challenges. The increasing numbers of patients who have received treatment for gynaecological cancer in conjunction with rising survival rates mean that the number of patients on follow-up is rising. A significant amount of medical, nursing and administrative time is spent on arranging and undertaking potentially unnecessary medical reviews. The unit cost for a non-admitted consultant-led, face-to-face, follow-up appointment in gynaecology oncology for the year 2014–2015 was £168 [30]. We estimate that in Wales, the National Health Service (NHS) cost of these routine follow-up appointments, excluding the cost of any tests ordered, is in excess of £1 million per annum based on current survival rates and national follow-up policies. This is in addition to any societal costs such as time taken from work to attend clinics and additional childcare costs.

### Alternative approaches to follow-up

In response to these challenges, a range of additional, alternative or supplementary approaches have been developed. These include risk-stratified care pathways, nurse-led clinics, telephone follow-up, reduced frequency of follow-up and remote surveillance strategies where biomarker or radiological follow-up is key. The National Cancer Survivorship Initiative [31] recommends a stratified approach to cancer follow-up care as opposed to the current traditional pathway. The NHS in England is piloting this risk-stratified approach that divides cancer patients into three groups: complex and requiring continued hospital care; shared care, for patients that require hospital care supplemented by education and support; and a self-care group that can be discharged from routine hospital follow-up [32]. However, the criteria for these groups are not yet fully defined and neither is the proportion of patients that will fall into each. Furthermore, there is as yet no evidence that this approach is superior to standard care or is the best alternative. We have recently undertaken a national survey of clinical practice in follow-up in all gynaecological cancers [33] which reported that a wide range of follow-up approaches are used across the UK despite there being little evidence that they lead to better outcomes for patients or are more cost-effective. Although the networks reported a wide range of practice in relation to tests and frequency of review, the survey confirmed that hospital-based, medical review remains the standard approach. A minority used nurse-led or telephone follow-up, and general practitioners (GPs) were rarely involved in routine care.

We propose an approach that aims to provide nurse-led telephone follow-up care for patients. Investigations into patterns of post-treatment cancer follow-up should assess recovery from treatment toxicity and social and psychological rehabilitation as well as health economics and the detection of relapse. Care should also be individualised so that patients can have the information they need as well as having their individual problems identified and managed. There is a pressing need for the NHS to develop patterns of care for patients who have had treatment for cancer that will address their needs, maximise their QoL and allow timely diagnosis of relapse yet uses NHS resources in a cost-effective manner. It is also important to convince patients, doctors and health service managers that this new approach can be adopted without any adverse effect on survival of patients.

### Purpose and scope

This study will evaluate the feasibility of a nurse-led needs assessment in the gynaecology cancer setting in North Wales and its utility to health care professionals when making decisions about supportive care, compared to disease- and site-matched patients not receiving the nurse-led needs assessment. The nurse-led intervention will be known as Optimal Personalised Care After Treatment for Gynaecological cancer (OPCAT-G) and will comprise patient education, patient empowerment and protocol-based, structured needs assessment undertaken with Gynae Oncology clinical nurse specialists (CNSs) by telephone. Patients will receive an initial structured telephone interview with a gynaecological CNS and a booklet including information on symptoms of recurrence and possible long-term physical and psychological side-effects of treatment. Information will also be given to patients on how they can contact the clinical team if they have concerns or symptoms; otherwise, they will receive routine telephone contact 6 months later. The telephone follow-up will involve a structured interview whereby patients’ unmet needs will be identified and patients will receive appropriate referral(s). The new approach will maintain regular contact with patients but will not involve routine hospital, outpatient attendance. The aim of this follow-up programme is to manage any long-term effects from treatment, to reassure the patient that the cancer remains in remission and if relapse occurs, to detect and treat it early.

This protocol falls within a larger body of work which includes a national survey relating to current practice of follow-up for gynaecological cancer patients in the UK [30], a BCUHB wide audit (headed by SL) of gynaecological cancer patients to establish key parameters in relation to recurrence and a small feasibility trial of a short-form needs assessment tool developed by one co-author (VM) and colleagues. Funding from Tenovus Cancer Care has been received for a Ph.D. student (LT, supervised by RTE, NS, VM) to explore work relating to patient and caregivers’ perspectives and preferences for different models of follow-up care [34]. Finally, we are currently conducting a systematic literature review to provide an up-to-date evaluation of the available evidence for the different strategies of follow-up after endometrial and vulval cancer. This body of work aims to show the wide applicability of the proposed intervention, whilst using this study as an exemplar of the methodology.

This study will focus on gynaecological cancer but will link with similar studies being developed in North Wales that will look at other exemplars, particularly prostate cancer (TOPCAT-P; ISRCTN34516019). The studies will be independent but will share expertise and co-investigators to develop a body of expertise relating the clinical research in this area.

## Methods/design

### Aim

The primary aim of the current study is to evaluate the feasibility of conducting a randomised trial comparing nurse-led telephone follow-up with standard, hospital-based, medical follow-up. Feasibility will be determined by the ability to recruit and retain patients to the study the ability to collect regular data and to evaluate the acceptability of implementing this new intervention.

The secondary aim of this feasibility study is to gain knowledge of standard deviations and effect sizes on the study outcome measures to inform the power calculation for a future full trial.

The final aim is to pilot the statistical and health economics analysis that would be required within a future full trial that will ultimately determine the effectiveness and cost-effectiveness of the new nurse-led telephone follow-up approach.

### Design

The current study will be a parallel-group randomised controlled feasibility trial design comparing nurse-led intervention (treatment group) with standard care (control group) to assess recruitment and retention rates and acceptability of randomisation and to inform the sample size calculation for a future trial.

### Participants

#### Inclusion criteria

We propose to recruit a cohort of female patients who have completed treatment for cervical, endometrial, epithelial ovarian, or vulval cancer within the last 3 months in BCUHB in North Wales. Patients who have completed treatment for fallopian tube and primary peritoneal carcinoma will also be included. The cohort will be identified through the regional gynaecological cancer multidisciplinary team meeting (MDT) records and will consist of patients who are considered fit for taking part in the trial and able to give informed consent, as assessed by the MDT. Patients may have received surgery, chemotherapy, radiotherapy or a combination of these. At the time of entry, patients in the view of their treating consultant will not have a definite need for continued hospital-based care.

#### Exclusion criteria

Patients having had treatment for sarcoma, germ cell tumour, borderline tumours or choriocarcinoma will be excluded as these women tend to require specific and/or more intense follow-up often with serial imaging or tumour markers. Patients requiring ongoing treatment will also not be included in the study. The study will not include patients who do not have the capacity to give informed consent or who are deemed to be unable to take part in the trial (e.g. severe learning/mental disability, severe mental health problems). Patients who are not able to understand Welsh or English will also be excluded.

### Sample size

We estimate 30% will not fit the inclusion criteria whilst an unknown proportion of the remainder will not enter the study, either through not wishing to consent or for other reasons. The extent of patient acceptability is unknown but for planning purposes, we will assume 50% acceptance. Assuming a throughput of approximately 150 newly diagnosed cases, we hope to randomise 50 participants from the recruiting centres into the study during a period of 6 months. It is thought this would be sufficient to inform a sample size of a future full trial [35] and enable a reasonably diverse group to fully assess the acceptability of the trial.

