### Recruitment

All patients will be recruited from three hospitals in the North Wales Cancer Network: Ysbyty Gwynedd, Ysbyty Glan Clwyd, and Ysbyty Maelor. The research nurse and three clinical nurse specialists (CNSs) will identify women from the hospital databases, in line with the inclusion and exclusion criteria above. Eligible patients will be approached by the clinic medical team and/or by the research nurse/CNS and will be invited to take part in the study. Patients will be given a participant information sheet at their end-of-treatment visit and will have until their follow-up appointment to consider the study (usually around 6 weeks), and those who would like to participate will have the opportunity to contact the research nurse by phone or email for more information before their follow-up appointment. Patients will be informed that if they agree to participate, they will be randomly assigned to one of the two treatment groups, both receiving slightly different modes of follow-up support. After agreeing to take part in the study, patients will give written consent at their 3-month routine follow-up appointment.

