### Trial status

The TOPCAT-G study started in July 2014, screening began in September 2015 giving a recruitment period of November 2015 to the end of April 2016. Follow-ups will continue until October 2016, and the trial is due to end in January 2017.

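### The target of 50 randomised in 6 months rests on about 150 new cases, but the Background's own counts support about 117 to 125, or roughly 41 to 44 randomised

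*Protocol article*

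**What the plan says.** The Sample size section sets out a recruitment funnel.

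- Eligibility: "We estimate 30% will not fit the inclusion criteria".
- Consent: "for planning purposes, we will assume 50% acceptance".
- Case flow and target: "Assuming a throughput of approximately 150 newly diagnosed cases, we hope to randomise 50 participants from the recruiting centres", and the sentence continues "into the study during a period of 6 months".

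The section then judges this number adequate to inform the size of a full trial and to bring in a reasonably diverse group. It gives no source for the 150 and attaches no period to it.

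The Background reports the local case load of the three hospitals that make up the health board: "with 92 ovarian cancer, 107 endometrial cancer and 35 cervical cancer newly diagnosed in 2014". The Recruitment section draws on the same hospitals: "All patients will be recruited from three hospitals in the North Wales Cancer Network". The Trial status section confirms a six-month window, "giving a recruitment period of November 2015 to the end of April 2016".

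**The concern.** The Sample size section and the Background describe the same catchment but imply different case loads. About 150 cases in six months corresponds to 300 a year, whereas the Background lists 234 a year. If the lower figure is right, the plan's own eligibility and acceptance rates do not produce 50 participants in the stated window.

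What is at stake is the sufficiency claim. The article relies on this sample for standard deviations and effect sizes to plan the full trial, and it calls the number adequate on the basis of 50.

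**Working it through.** **Inputs**

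- Assumed throughput: 150 (Sample size).
- Eligible: 1 − 0.30 = 0.70 (Sample size).
- Acceptance: 0.50 (Sample size).
- Recruitment window: 6 months (Sample size; November 2015 to end of April 2016 in Trial status).
- Local new cases in 2014: 92 + 107 + 35 = 234 (Background).
- UK annual counts, used only for the vulval allowance: "endometrial (c. 8500 per year), ovarian (c. 7000 per year), cervical (c. 3000 per year) and vulval (c. 1200 per year" (Background).

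**Formula:** expected randomised = cases in window × 0.70 × 0.50 = cases × 0.35.

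**1. Reproduce the plan's figure.** 150 × 0.35 = 52.5, which agrees with a target rounded to 50. If 150 were an annual count, six months would hold 75 cases and 75 × 0.35 = 26. Only the six-month reading gives 50.

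**2. Use the Background's case load.** 234 / 2 = 117 cases in six months, and 117 × 0.35 = 40.95, about 41. This step uses no outside figure.

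**3. Allow for vulval cancer.** It is eligible but has no local count. The UK ratio is 1200 / (8500 + 7000 + 3000) = 6.5%. Applied locally, as an assumption, it adds 234 × 1200 / 18,500 = 15.2 cases a year. Then (234 + 15.2) / 2 = 124.6 and 124.6 × 0.35 = 43.6, about 44.

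**4. Size of the gap**

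| | Listed sites only | With vulval allowance |
|---|---|---|
| Cases in 6 months | 117 | 124.6 |
| Expected randomised | 41 | 44 |
| Shortfall against 50 | 9 (18%) | 6 (12%) |
| Excess of 150 over cases in 6 months | 150 / 117 = 1.28, so 28% | 150 / 124.6 = 1.20, so 20% |
| Acceptance needed for 50 | 50 / (117 × 0.70) = 61% | 50 / (124.6 × 0.70) = 57% |
| Months needed for 50 | 50 / (40.95 / 6) = 7.3 | 50 / (43.6 / 6) = 6.9 |

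**5. How many uncounted cases would close it?** Exactly 50 needs 50 / 0.35 = 143 cases in six months, or 286 a year. That is 52 more than the 234 listed. A full 150 in six months needs 300 − 234 = 66 more. The vulval allowance supplies about 15.

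**6. Chance of reaching 50 all the same.** If the number randomised is treated as Poisson with mean 40.95 or 43.6, the probability of 50 or more is about 9% or 18%. Fixing the number eligible at 82 or 87 with exactly 50% acceptance (binomial) gives 3% or 10%. That is too narrow, because case numbers vary too. Neither calculation allows for uncertainty in acceptance, which the protocol calls unknown.

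**The case against.** **The window may be longer than six months.** The six months attach to randomising, not explicitly to the 150. Screening began in September 2015, so eight months to the end of April 2016 would hold 234 × 8 / 12 = 156 cases and yield 55. A nine-month pool, built from the criterion of treatment completed in the last three months, would hold 175.5 cases and yield 61. These readings are possible but not stated. Consent and randomisation take place at the 3-month appointment, so a six-month recruitment period takes in about six months of women finishing treatment. The information sheet is given at the end-of-treatment visit, so screening before November looks like lead time rather than extra accrual.

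**The bases may differ.** Fallopian tube and primary peritoneal cancers are eligible but not separately counted. The 150 might also include the excluded tumour types, in which case taking the full 30% off the 234 removes some ineligible patients twice. At 50% acceptance, 50 would be reached from 117 cases if 85% were eligible (50 / 58.5), or from 124.6 if 80% were (50 / 62.3). The article does not settle this, so 41 to 44 is an estimate that depends on assumptions. However, nothing in the text supports the roughly 52 additional cases a year needed at the stated 30%.

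**The consequences are limited.** A reader might infer that a shortfall would be mistaken for poor acceptability. The definitions do not allow that: the recruitment rate is consenters over eligible patients invited, so 41 of 82 and 52 of 105 both give about 50%. A reader might also infer that a stated precision is lost. None is stated; the section says only that the number is thought sufficient, and nothing shows that 41 to 44 would not be. The wording is tentative, and the full protocol may give the source of the 150. These points stand and lower the severity.

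**Conclusion.** The inconsistency between the Sample size section and the Background holds. On the plan's own eligibility and acceptance rates, the local case load supports about 41 randomised in six months, or about 44 with the vulval allowance. That is some 6 to 9 short of 50.

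The result assumes that 2014 incidence is stable, that treatment completions track diagnoses, that few other eligible cases go uncounted, and that the 150 refers to the six-month window. The last follows from the target itself, since an annual reading gives only 26.

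The point is of moderate severity. No decision rule, primary outcome definition or analysis changes. It is a planned size that the article's own inputs do not deliver, together with a sufficiency claim tied to that size.

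**What to change.** Reconcile the Sample size section with the Background in one of two ways.

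- If a documented basis for the 150 exists, state its source, the tumour types it covers and the period it refers to.
- Otherwise, restate throughput as about 117 to 125 cases per six months and the expected number randomised as about 41 to 44. Mark the vulval allowance as an assumption, and restate the claim of sufficiency for that number.

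Keeping 50 by recruiting for about 7 months is possible only if the timetable moves as well. A woman randomised at three months post-treatment at the end of April 2016 reaches the 9-month endpoint in October 2016, which is when follow-up is due to stop.

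The cost of restating is one rewritten paragraph and a slightly less favourable expected number. It needs no extra patients and no change to the analysis.
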